#### HR and HRV

HRV, which is influenced by stress, reflects the autonomic nervous system’s level of arousal and can serve as an objective measure of psychological well-being and experienced stress.^33^ HR and HRV will be continuously recorded throughout the visits using the Actiheart device (CamNtech, Papworth, UK). Actiheart is a validated instrument that reliably measures HR and interbeat interval (IBI).^34^ We will use the Actiheart model 4 that consists of two monitors which will be placed on the midsternal line and on the left thorax on the level of the third intercostal space.

To ensure stable baseline and recovery measurements, participants will be asked to remain seated in a resting position for 2 min before and after the EEG recording and the snack. The duration will be timed using a stopwatch to standardise measurement periods.

The commercial Actiheart Software Kubios HRV Premium (V.3.5.0) software^35^ will be used for data cleaning and transformation to export IBI. Kubios is a software for HRV analysis and computes time-domain and frequency-domain parameters.^36^ Time-domain parameters are calculated from the IBI and inform about variability between successive R-peaks. The frequency domain measures estimate the distribution of absolute and relative power into four frequency bands. Time-domain variables to be included are mean HR, the root mean square of successive differences between normal heartbeats, and the percentage of successive RR intervals that differ by more than 50 ms (pNN50). For frequency-domain variables, we will include high-frequency (HF) and low-frequency (LF), both in absolute units (ms^2^) and normalised units, as well as the LFHF ratio.

#### Anthropometric measurements and body composition

Participants’ body weight and height will be measured using a regularly calibrated electronic scale (Seca Model 7017021094, Hamburg, Germany). Body composition will be measured using bioelectrical impedance analysis (BIA). Low-voltage electrical currents will be applied through electrodes placed on the extremities. The BIA 101 (Akern, Italy, medically certified) measures tissue resistance and reactance using four electrodes: two on the right hand and two on the right foot, separated by 3–4 cm. The InBody S10 system is based on a 4-compartment model, estimating total body water, protein, mineral and body fat and uses electrodes on all four extremities. Measures of interest will include fat mass, fat-free mass, visceral fat surface and the percentage of these measures related to body weight as well as calculated waist circumference and phase angle.

#### Snack and objective eating behaviour

During both study visits, participants will be offered eight snacks of different textures and levels of crunchiness during a snack break. The snacks vary in fat and carbohydrate content with two snacks from each food category described above. At both visits, participants will be presented with potato chips (10 g), milk chocolate (25 g), peanuts (20 g), almonds (20 g), pretzels (15 g), gummy bears (25 g), tomatoes (50 g) and blueberries (50 g) corresponding to one portion of each snack item. All snacks are safe and appropriate for pregnancy and fresh fruits and vegetables will be thoroughly washed and prepared according to standard pregnancy food-safety guidelines. Participants will be informed that they can eat as much or as little as they want, with no expectations regarding completion. The type and quantity of snacks consumed, as well as the time spent eating, will be recorded by the study team. Once participants indicate they have finished eating, they will be asked regarding their perceived eating duration and eating speed.

Objective eating behaviour will be assessed using an eating behaviour recognition device, which uses an accelerometer (ADXL362) and contact microphone (CM-01B) positioned over the mastoid bone to detect chewing-related motion and vibrations transmitted through the mandible during eating. During the standardised snack, the device will continuously record chewing-related signals to derive objective eating behaviour measures, including eating onset latency (seconds), eating duration (minutes), eating rate (event/time) and other temporal characteristics of eating behaviour. These objective measures will complement the observed snack intake (type and quantity consumed) and participants’ self-reported eating speed and eating duration. They will be used to investigate whether objectively measured eating behaviour is associated with neural responses to visual food cues measured by EEG and behavioural responses measured by the Go/NoGo task, and whether these associations differ between women with NW and those with OW/OB. This eating behaviour recognition device has previously demonstrated high accuracy for automated eating detection using chewing-related motion and vibration signals.^37^

#### Glycated haemoglobin

HbA1c levels (%) will be measured for each participant at both study visits from a capillary blood sample using the validated Afinion 2 point-of-care analyser.^38^ This device uses a chemical photometric method with boronate conjugation.^39^ The measure represents the mean glucose levels over the last 2–3 months and will be used as a continuous variable.

#### Chester step test

The CST will be used to estimate the participants’ cardiorespiratory fitness (VO_2_max indicated in mL/kg/min). The CST is a multistage submaximal test that has demonstrated reasonable validity against indirect calorimetry to predict cardiorespiratory capacity.^40^ From the CST results, a standardised equation will be used to estimate the VO_2_max.^40^ After a 30 s familiarisation, participants will step up and down to an audiotape starting at 15 steps/min, increasing by five steps/min every 2 min, for a maximum of 10 min. The step height will be set at 15 cm. HR and rate of perceived exertion (RPE, according to Borg’s scale) will be monitored at the end of every 2-minute stage. The test will be stopped at 80% of the estimated HRmax (220 – age), RPE ≥15, or when participants show signs of distress.

#### Eating behaviour and hunger

Eating behaviour will be assessed using the French IES-2. This is a validated self-reported questionnaire that assesses participants’ tendency to rely on physical hunger and satiety cues and has demonstrated good psychometric properties.^41
42^ The IES-2 consists of 18 items across 3 subscales: Reliance on Hunger and Satiety Cues (RHSC, six items), Eating for Physical rather than Emotional Reasons (EPR, eight items) and Unconditional Permission to Eat (UPE, four items). Items are scored on a 5-point Likert from 1=‘strongly agree’ to 5=‘strongly disagree’, with subscale scores ranging from 1 to 5. For the RHSC subscale, higher scores indicate greater trust in internal hunger and fullness signals, while lower scores indicate reduced capacity to regulate food intake based on these cues. For the EPR subscale, higher scores indicate eating in response to physical hunger, whereas lower scores reflect eating for emotional reasons. For the UPE subscale, higher scores indicate unconditional permission to eat, whereas lower scores indicate restrictive eating.

Three dimensions of eating behaviour will be assessed using the TFEQ-R18. These dimensions include cognitive restraint (six items), uncontrolled eating (nine items) and emotional eating (three items). Items will be scored on a 4-point Likert scale ranging from 1=‘almost always’ to 4=’never’. Raw scores will be calculated for each subscale and then transformed into percentage scores, representing the relative proportion of the highest possible raw scores (0 to 100). The revised questionnaire has been shown to have good psychometric properties.^43^

Current food cravings will be assessed through the FCQ-s which will evaluate the intensity and presence of cravings at a given time in response to specific situations or emotional and physiological cues. The 15 items will be scored on a 5-point Likert scale ranging from 1=‘strongly disagree’ to 5=‘strongly agree’. The total score will represent the current food craving state, with higher scores indicating more intense current food cravings. The French version was translated and used in previous research by our collaborators.^44^

Current food ‘wanting’ will be assessed using the item ‘How much do you want this food?’ rated from 0 to 100 on a VAS. Participants will provide ratings for 24 food images of varying fat and carbohydrate content. This will take place immediately after the EEG recording.

Current hunger will be assessed with a single item ‘What is your current level of hunger?’ rated on a 0 to 100 VAS, with 0=‘not hungry at all’ and 100=‘very hungry’.

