### Secondary outcomes

The secondary outcomes include weight, glycated haemoglobin (HbA1c) and body composition. We will also investigate eating behaviour through self-reported questionnaires including food cravings (Food Craving Questionnaire-state, FCQ-s), intuitive eating (French Intuitive Eating Scale-2, IES-2), external, emotional eating and cognitive restriction (Three-Factor Eating Questionnaire-Revised 18, TFEQ-R18). We will measure eating rate using an objective eating behaviour recognition device and subjective questions (self-reported eating rate). We will measure the current mood (Adapted Multidimensional Mood Scale, A-MMS), current level of perceived stress (single-item) and depressive symptoms (Edinburgh Postnatal Depression Scale, EPDS). We will measure heart rate (HR) and heart rate variability (HRV) using an Actiheart. We will finally investigate aerobic fitness using the Chester Step Test (CST).

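### The printed IES-2 anchors conflict with the stated direction of its scores unless items are reversed, and the TFEQ-R18 percentage as defined runs from 25 to 100, not 0 to 100

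*Protocol article*

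**What the plan says.** All of the scoring text is in the protocol article under Eating behaviour and hunger.

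- **IES-2 structure and coding.** "The IES-2 consists of 18 items across 3 subscales": RHSC with six items, EPR with eight and UPE with four. The coding is "Items are scored on a 5-point Likert from 1=‘strongly agree’ to 5=‘strongly disagree’, with subscale scores ranging from 1 to 5".
- **IES-2 meaning.** For the first subscale the text says "For the RHSC subscale, higher scores indicate greater trust in internal hunger and fullness signals". For the second it is equally explicit: "For the EPR subscale, higher scores indicate eating in response to physical hunger, whereas lower scores reflect eating for emotional reasons". UPE is read the same way, with a low score taken as a sign of restriction. No recoding or reverse-scored item is mentioned.
- **TFEQ-R18.** Cognitive restraint has six items, uncontrolled eating nine and emotional eating three. Each item is scored from 1 (almost always) to 4 (never). Raw subscale scores are then "transformed into percentage scores, representing the relative proportion of the highest possible raw scores (0 to 100". The section does not say what a high score on any TFEQ-R18 subscale means.
- **FCQ-S, for comparison.** In the same section its items run from 1 for strong disagreement to 5 for strong agreement, and a high total means more intense craving.
- **Outcome list.** Under Secondary outcomes, the TFEQ-R18 is said to measure "external, emotional eating and cognitive restriction".

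**The concern.** The article prints anchors, score ranges, a transformation and score meanings, and these do not fit together. On the IES-2, a participant who strongly agrees with statements expressing trust in her hunger and fullness signals gets the lowest code, while the text reads low scores as low trust. The TFEQ-R18 transformation cannot produce its stated range. One TFEQ-R18 outcome has a different name in the two places where it appears.

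The Aims make the relationship of brain responses with eating behaviour a secondary objective, and the Statistical analysis plan section gives intuitive eating as an example of a variable to be related to brain responses by regression. In such an analysis the sign of the coefficient is most of the finding. Data collection and study visits says that the first participant has already attended, so responses are already being recorded under some coding.

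**Working it through.** **Inputs.** Item counts, anchors, stated ranges and stated meanings, all from Eating behaviour and hunger. Item wording is not in the document, so three cases are considered for it.

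**1. IES-2 range.** With the subscale score as the item mean:
- RHSC: 6/6 = 1 to 30/6 = 5
- EPR: 8/8 = 1 to 40/8 = 5
- UPE: 4/4 = 1 to 20/4 = 5

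The stated range of 1 to 5 is reproduced. Reversing items (6−x) leaves it unchanged, so a range check would not reveal a wrong direction.

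**2. IES-2 direction, printed coding with no reversal.**
- *All items worded in the direction of the subscale name.* Strong agreement with all six RHSC items scores 6×1/6 = 1, which the text reads as low trust. With 6−x the score is 5. Since mean(6−x) = 6 − mean(x), every correlation or slope involving the subscale changes sign and keeps its size.
- *Half worded each way* (assumed, eight items). A participant at the high extreme of the trait scores (4×1 + 4×5)/8 = 3. One at the low extreme scores (4×5 + 4×1)/8 = 3. The score hardly separates them, so associations are attenuated, not flipped.
- *All items worded against the name.* The printed coding already agrees with the stated meaning.

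One simulated data set of 94 participants, with assumed effect sizes, illustrates the three cases:

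| Item wording | r, scored to match stated meaning | r, coding as printed |
|---|---|---|
| All with the name (6 items) | +0.38 | −0.38 |
| Half and half (8 items) | +0.45 | −0.05 |
| All against the name (8 items) | +0.44 | +0.44 |

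The pattern matters here. The values themselves are not predictions for this study.

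**3. TFEQ-R18 range.** As defined, percentage = 100×raw/max.

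| Subscale | Raw range | 100×raw/max | 100×(raw−min)/(max−min) |
|---|---|---|---|
| Cognitive restraint (6 items) | 6–24 | 25–100 | 0–100 |
| Uncontrolled eating (9 items) | 9–36 | 25–100 | 0–100 |
| Emotional eating (3 items) | 3–12 | 25–100 | 0–100 |

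The stated 0 to 100 is not reproduced. It needs the min–max form, or items coded 0–3. Example: a six-item raw score of 12 is 12/24 = 50% as defined, but (12−6)/18 = 33.3% in min–max form.

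**4. Effect of the TFEQ-R18 formula.** Let A be the score as defined and B the min–max score. Then A = 25 + 0.75×B (check: 25 + 0.75×33.3 = 50). The relation is linear with positive slope, so signs, correlations and p-values are the same; the simulation gave r = 0.404 for both. Compared with B, using A multiplies a regression coefficient by 1/0.75 = 4/3 when the score is a predictor and by 0.75 when it is the outcome. Reported means shift as well.

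**5. TFEQ-R18 direction.** If items describe the named behaviour, answering never to all nine uncontrolled-eating items gives raw 36, or 100%. That sits awkwardly with the subscale name, but the text gives no meaning that it contradicts.

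**The case against.** The strongest reply on the IES-2 is that the target is fixed: the article says what high and low mean for all three subscales. An analyst working to those meanings, with the questionnaire's scoring key, would orient the scores correctly. The anchors could be the response format as presented, or a transposition in the text, and a reversal key is detail that an article may leave to a fuller document. This stands in part. Nothing shows that data will be scored the wrong way. But the point is not that a key is missing. The section prints a coding rule that, taken with its own interpretation, is inconsistent for any subscale worded in the direction of its name. The FCQ-S description beside it shows the opposite anchors with the same reading of high scores.

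On the TFEQ-R18, the reply is that the stated range shows the intended scale and the formula has no inferential effect. It is right that no test changes. Means and coefficients would still be reported in units that depend on which reading is used. The mismatch between 'external' and 'uncontrolled' is one of labels, since the measures section makes clear which three scores will be computed.

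A reader might infer two stronger claims. The first is that the TFEQ-R18 coding also runs opposite to its stated meaning. It cannot, because no meaning is stated. The second is that the eating-behaviour associations in general would change sign. The document does not support this: the TFEQ-R18 formula changes no sign, and for the IES-2 the result depends on item wording that is not given. The FCQ-S is consistently scored, and the wanting ratings, snack intake and device measures are untouched.

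**Conclusion.** Two statements in the scoring section need correction.

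1. The IES-2 anchors conflict with the stated score meanings unless items are reversed, and no reversal is stated. If the printed rule is followed, RHSC is the subscale most plausibly scored backwards, with r becoming −r. EPR and UPE could be reversed, attenuated or correct, depending on item wording. This rests on the assumption that RHSC items are worded in the direction of the subscale name. The document does not show which of the anchors or an unstated recode was intended.
2. The TFEQ-R18 percentage as defined has a minimum of 25, not 0. This needs no assumption beyond the printed item codes. It affects means and coefficient units only. The unstated direction of the subscales is a separate gap in interpretation.

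If the working script already scores both instruments properly, this is an error of text only. The primary EEG and Go/NoGo outcomes and the sample size are unaffected. The correction is still worth making, because an undetected reversal would give a secondary conclusion in the wrong direction.

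**What to change.** - **IES-2:** reconcile the anchors with the stated score direction. Either correct the anchors, or keep them and specify the recode; in both cases list the reverse-scored items.
- **TFEQ-R18:** define each subscale score as 100×(raw−min)/(max−min), and state what a high score means for each of the three subscales, with any recoding needed.
- **Outcome names:** reconcile 'external' eating under Secondary outcomes with 'uncontrolled' eating under Eating behaviour and hunger.
- **Check before analysis:** compare the scoring script and the export coding of data already collected with the corrected text. Scoring an invented respondent who strongly agrees with every RHSC item, and one who answers never to every uncontrolled-eating item, would show the direction at once for items that need no individual reversal.

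The cost is a text correction and a short check of the script. No new data are needed.

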#### Mental health, mood, and stress

Depressive symptoms during pregnancy will be assessed using the EPDS, a validated 10-item self-reported questionnaire. Each item will be rated on a 4-point Likert scale with higher scores indicating greater depressive symptoms, and the total scores range from 0 to 30 points. This is a validated self-reported questionnaire that demonstrates good psychometric properties in the perinatal period.^45^

Current mood will be assessed using an adapted version of the Multidimensional Mood Scale, consisting of eight bipolar items.^46
47^ Each item will be presented on a 0 to 100 bipolar scale between opposing mood states (eg, tired vs awake), with higher values indicating a mood closer to the right-hand pole. Responses will be provided with a slider from the start position at 50. In addition, the feelings of fear, joy, sadness, and anger were assessed using a VAS (from 0 to 100).

Current level of perceived stress will be assessed with a single item ‘What is your current level of stress?’ rated on a 0 to 100 VAS with 0=‘not stressed at all’ and 100=‘very stressed’.

### Data management and statistical analyses

#### Sample size calculation

The sample size estimation was informed by previous EEG studies of similar design outside of the perinatal context,^23
28
48^ as well as internal pilot data from our group. For EEG outcomes, preliminary data from our previous study (CER-VD 2021-01976) showed a significant fat x group interaction in global field power (GFP) (ηp²=0.103, F(1,37)=4.237, p=0.047; Cohen’s f=0.34). Power analysis assuming an alpha level of 0.05 and 80% power indicated that 35 participants per group were needed. For the Go/NoGo smartphone task used in a different context, pilot data demonstrated group differences in RTs of 550 ms±63 in women with NW and 450 ms±63 in women with OW/OB, at least eight participants per group would be required to detect significant differences in RT assuming an alpha level of 0.05 and 80% power.

Participants diagnosed with GDM at the second visit (approximately 16%) will be excluded in sensitivity analyses. To account for these exclusions and an additional anticipated dropout of 10%–20%, a total of 94 participants (47 per group) with valid data will be recruited. This is expected to result in approximately 37 participants per group at the second visit with valid data, corresponding to the highest requirement derived from our calculations.

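### The expected 37 per group at visit 2 does not follow from 47 per group after both stated losses, which leave about 32–36; the shortfall touches only the GDM-excluded sensitivity analysis

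*Protocol article*

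**What the plan says.** All the relevant statements are in the protocol article, section Sample size calculation.

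- EEG requirement: the planning effect is a fat-by-group interaction in global field power from an earlier study ("ηp²=0.103, F(1,37)=4.237, p=0.047; Cohen’s f=0.34"). From it, "Power analysis assuming an alpha level of 0.05 and 80% power indicated that 35 participants per group were needed". The Go/NoGo reaction-time calculation asks for eight per group.
- First loss: "Participants diagnosed with GDM at the second visit (approximately 16%) will be excluded in sensitivity analyses".
- Second loss and target: the plan allows for those exclusions and "an additional anticipated dropout of 10%–20%, a total of 94 participants (47 per group) with valid data will be recruited".
- Result: "This is expected to result in approximately 37 participants per group at the second visit with valid data", which the same sentence describes as "corresponding to the highest requirement derived from our calculations".

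Two other sections bear on scope. Study population and eligibility criteria says that the 94 participants will have valid primary-outcome data. Aims lists change from early to late pregnancy as a secondary objective.

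**The concern.** The second loss is described as additional to the first, and 47 per group is presented as absorbing both. A reader will therefore take 37 as what remains after GDM exclusion and dropout, and will conclude that even this reduced set exceeds what 80% power needs. If 37 is too high for that set, the reassurance is wrong for the analysis to which it most naturally refers.

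There is a second mismatch inside the same sentence. It equates 37 with the largest requirement derived, but the only requirements in the section are 35 and eight.

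Behind both lies a merging of two analysis sets. GDM cases leave only in sensitivity analyses, so visit 2 has a larger set with them and a smaller set without them. One number cannot describe both.

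**Working it through.** **Inputs (all from Sample size calculation).** 47 recruited per group; GDM exclusion g = 0.16; dropout d = 0.10 to 0.20; f = 0.34; alpha 0.05; power 80%; required n = 35 (EEG) and 8 (Go/NoGo). Sidedness is not stated; an F test is used here.

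**Step 1: reproduce the plan's requirements.** f = √(0.103/0.897) = 0.339, which rounds to the stated 0.34. For two groups of n, power comes from the noncentral F distribution with 1 and 2n−2 degrees of freedom and noncentrality 2n·f². At n = 35 the noncentrality is 70×0.34² = 8.09 and power is 80.1%, so 35 reproduces. With the unrounded f, power at 35 is 79.8% and 36 are needed, which is still not 37. For Go/NoGo (difference 100 ms, SD 63), exact t power is 77.8% at seven per group and 83.9% at eight, so eight reproduces.

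**Step 2: apply the stated losses to 47 per group** (power at f = 0.34):

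| Dropout d | Both losses, sequential: 47×0.84×(1−d) | Power | Both losses, added: 47×(1−0.16−d) | Power | Dropout only, GDM kept: 47×(1−d) | Power |
|---|---|---|---|---|---|---|
| 10% | 35.5 | 80.7% | 34.8 | 79.8% | 42.3 | 87.1% |
| 15% | 33.6 | 78.4% | 32.4 | 76.9% | 40.0 | 85.1% |
| 20% | 31.6 | 75.8% | 30.1 | 73.7% | 37.6 | 82.9% |

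For reference, 37 per group gives 82.3% and 47 per group (visit 1) about 90%.

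**Step 3: what 37 would need.** After GDM exclusion 47×0.84 = 39.48 remain, so 37 implies dropout of 1 − 37/39.48 = 6.3% (5.3% if losses are added: 0.84 − 37/47). Both lie below the plan's lower bound of 10%. The one entry in the table that matches 37 is 20% dropout with no GDM exclusion, 37.6.

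**Step 4: where the GDM-excluded set drops below 35.** Sequentially, at d = 1 − 35/39.48 = 11.3%. With losses added, at d = 0.84 − 35/47 = 9.5%.

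**Step 5: where 47 itself fits.** 35/(0.84×0.90) = 46.3, which rounds up to 47. The recruitment target therefore secures 35 per group after both losses at the lower end of the dropout range. At the upper end it would take 35/(0.84×0.80) = 52.1, that is 53 per group.

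**The case against.** The best defence is that 37 was meant as the visit-2 number before GDM exclusion at the worst dropout. 47×0.80 = 37.6 fits, and on that reading the figure is conservative and exceeds 35. This may well be how it arose. But the wording ties the 47, and hence the result, to both losses, so the text as printed does not say it. Nor does this reading explain why 37 is called the highest requirement.

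It can also be said that the gap is small at the favourable end. At 10% dropout the sequential figure is 35.5, not far from approximately 37, and it still meets the requirement of 35 with 80.7% power. That stands. It does not help across the rest of the stated range.

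The sequential calculation is the more natural one, and this limits the size of the point. GDM status is taken at the second visit, so the 16% most plausibly applies to women who attend it. The figures of 30.1 per group and 73.7% power need the losses to be added, that is, 16% of all enrolled with no overlap between GDM and dropout. They should not be quoted as the expected lower bound without that assumption.

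A reader might infer that the study, or its main analyses, are underpowered. The documents do not support this. GDM exclusion is confined to sensitivity analyses, the main visit-2 set has 83–87% power for the planned effect, and visit 1 has about 90%. A reader might also expect the GDM exclusions to fall mainly on the overweight/obesity group, which the Aims section places at higher metabolic risk. That is plausible, but no GDM rate by group is given, so unequal loss can be noted only as an assumption.

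**Conclusion.** The stated figure is wrong as written. The two losses leave about 32–36 per group at visit 2 (31.6–35.5 sequentially; 30.1–34.8 if added), not 37, and the highest derived requirement is 35. For the GDM-excluded visit-2 sensitivity analysis, 80% power at f = 0.34 holds only up to about 11% dropout and falls to about 76% at 20%. No other analysis is affected, and the error does not by itself show that 94 participants are too few.

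The result rests on the document's own inputs, on GDM exclusion applying to women still in the study at visit 2, on equal loss in both groups, and on a two-group F test at alpha 0.05, which reproduces the plan's 35. This is a reporting error in the sample-size justification, not a flaw in the design.

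**What to change.** Replace the closing sentence of Sample size calculation with separate statements for the two visit-2 sets, for f = 0.34 and alpha 0.05:

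- **GDM cases retained (main visit-2 analysis):** about 38–42 per group at 20–10% dropout, power 83–87%.
- **GDM cases excluded (sensitivity analysis):** about 32–36 per group at 20–10% dropout, power 76–81%, stating that the 16% is applied to participants remaining after dropout.

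Compare both with the derived requirement of 35 and remove the statement that 37 is the highest requirement. Do not describe the GDM-excluded analysis as having 80% power beyond about 11% dropout. If wished, add that GDM exclusions may be unequal between groups, labelled as an assumption.

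The cost is a change of wording and one less favourable figure. No extra recruitment is needed. Only if the sponsor wanted 80% power for the GDM-excluded analysis at 20% dropout would the target have to rise, to 53 per group under the sequential calculation.
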